## Abstract

**Background:**

Efficient and effective strategies for treating chronic health conditions such as hypertension are particularly needed for under-resourced clinics such as Urban Indian Health Organizations (UIHOs).

**Objective:**

The objective of the Controlling Blood Pressure Trial is to assess the impact of an interactive voice response and text message (IVR-T) intervention compared with usual care among individuals with hypertension receiving care at a UIHO in Albuquerque, New Mexico. This manuscript presents the baseline characteristics of individuals enrolled in the trial and compares their characteristics with those in the hypertension registry who did not enroll in the trial.

**Methods:**

A hypertension registry developed from the clinic’s electronic health record was used for recruitment. Potentially eligible participants were contacted by letter and then by phone. Those who expressed interest completed an in-person baseline visit that included a baseline survey and blood pressure measurement using standardized procedures. Individuals randomized to the intervention group could opt to receive either automated text messages or automated phone calls in either English or Spanish. The messages include reminders of upcoming appointments at First Nations Community HealthSource, requests to reschedule recently missed appointments, monthly reminders to refill medications, and weekly motivational messages to encourage self-care, appointment keeping, and medication taking for hypertension. Individuals in the IVR-T arm could opt to nominate a care partner to also receive notices of upcoming and missed appointments. Individuals in the IVR-T arm were also offered a home blood pressure monitor. Follow-up visits will be conducted at 6 months and 12 months.

**Results:**

Over a 9.5-month period from April 2017 to January 2018, 295 participants were enrolled from a recruitment list of 1497 individuals. The enrolled cohort had a mean age of 53 years, was 25.1% (74/295) American Indian or Alaska Native and 51.9% (153/295) Hispanic, and 39.0% (115/295) had a baseline blood pressure greater than or equal to 140/90 mmHg. Overall, the differences between those enrolled in the trial and patients with hypertension who were ineligible, those who could not be reached, or those who chose not to enroll were minimal. Enrolled individuals had a slightly lower blood pressure (129/77 mmHg vs 132/79 mmHg; *P=*.04 for systolic blood pressure and *P*=.01 for diastolic blood pressure), were more likely to self-pay for their care (26% vs 10%; *P*<.001), and had a more recent primary care visit (164 days vs 231 days; *P*<.001). The enrolled cohort reported a high prevalence of poor health, low socioeconomic status, and high levels of basic material needs.

**Conclusions:**

The Controlling Blood Pressure Trial has successfully enrolled a representative sample of individuals receiving health care at a UIHO. Trial follow-up will conclude in February 2019.

**Trial Registration:**

ClinicalTrials.gov NCT03135405; http://clinicaltrials.gov/ct2/show/NCT03135405 (Archived by WebCite http://www.webcitation.org/76H2B4SO6)

**International Registered Report Identifier (IRRID):**

DERR1-10.2196/11794

## Introduction

### Background

American Indians and Alaska Natives (AI/ANs) face pervasive health disparities in comparison with other racial and ethnic groups in the United States. Although disparities in diabetes have received national attention, cardiovascular disease (CVD) remains the primary cause of mortality in AI/ANs as in other groups [1]. Interventions to prevent CVD in AI/ANs have historically focused on individuals with diabetes (eg, the Special Diabetes Program for Indians Healthy Heart Demonstration Project) [2], with few studies of interventions to prevent CVD among AI/ANs without diabetes. Successful CVD prevention for AI/ANs requires the engagement of health care systems dedicated to this population. The health care system for AI/ANs includes federally operated Indian Health Service (IHS) facilities, tribally operated facilities, and 33 Urban Indian Health Organizations (UIHOs) across the United States. All face unremitting challenges in funding and staffing that jeopardize their mission to provide culturally appropriate health care, outreach, and referral services for AI/AN. Strategies for treating chronic health conditions are particularly problematic in UIHOs. Although 71% of AI/ANs live in urban areas, UIHOs only receive 1% of the IHS budget [3,4].

Treatment of hypertension is a pillar of CVD prevention. Hypertension is the most common chronic health condition in the United States [5]. Uncontrolled hypertension increases the risk of myocardial infarction, stroke, kidney failure, and congestive heart failure [6]. Hypertension rates are high, levels of control are low, and disparities in care are evident in AI/AN populations [1,7-9]. Communication technologies that extend care to patients “where they are,” outside the clinical setting, can facilitate hypertension control [10]. Such outreach may be particularly important for AI/ANs and other vulnerable populations that face logistical and cost barriers to receiving office-based care.

Interactive Voice Response and Text Message (IVR-T) technology can be used to send targeted voice messages to landlines and voice or text messages to cell phones. IVR-T tools could improve hypertension care by sending reminders about appointments or medication refills, recalling individuals who have missed appointments, and providing educational and motivational messages [11]. Existing evidence suggests that such interventions can improve medication adherence [12-15], appointment keeping [16], and blood pressure control [14,17]. Randomized controlled trials (RCTs) of IVR-T interventions have demonstrated clinical benefit at a low marginal cost [18-21]. In resource-constrained UIHOs, IVR-T messages may substitute for costly and time-intensive personal outreach by staff members. In addition, home blood monitoring without additional support has been shown to have a modest effect of systolic blood pressure at 6 months, but little sustained effect [22,23].

### Objectives

The specific aim of the Controlling Blood Pressure Trial is to assess the impact of an IVR-T intervention compared with usual care among individuals with hypertension receiving care at a UIHO in Albuquerque, New Mexico. The primary study endpoint is change in mean systolic blood pressure between baseline and 12 months. Secondary endpoints include change in diastolic blood pressure, self-reported adherence, and the proportion of missed clinic appointments between intervention and control groups.

## Methods

### Study Setting

This pragmatic clinical trial is taking place at First Nations Community HealthSource (FNCH), a nonprofit, urban Indian community-based health and human services organization incorporated in 1972. The health center is authorized through Title V of P.L. 94-437, and subsequent amendments, of the Indian Health Care Improvement Act to improve the health of urban Indians. FNCH has expanded its mission to serve the greater community, without losing its fundamental basis for existence, and now provides primary medical care to urban AI/ANs and other socially disadvantaged residents of the Albuquerque, New Mexico area. In 1997, the center was designated as a Federally Qualified Health Center, and it is an Accreditation Association for Ambulatory Health Care (AAAHC)-Accredited Health Center and Medical Home. Approximately 40% of FNCH clients are AI/AN; Diné (Navajo) is the most common tribal affiliation. Many other clients served by FNCH are undocumented immigrants. Housing insecurity and homelessness are common. Most clients speak either English or Spanish as their primary language. FNCH has 3 campuses in close geographic proximity in southeastern Albuquerque. The medical clinic is staffed by physicians, nurse practitioners, and physician assistants with extensive support staff including public health nurses, diabetes educators, patient navigators, and on-site behavioral health clinicians. FNCH provides comprehensive primary medical, dental, behavioral health, and traditional healing and a range of preventive support services to address the health disparities experienced by its target population. Its mission is to provide a culturally competent, comprehensive health service delivery system integrating traditional values to enhance the physical, spiritual, emotional, and mental well-being of American Indian families and other underserved populations residing in Albuquerque and on tribal reservations.

The study team established an Advisory Council consisting of FNCH staff from pharmacy, public health nursing, and social services and 2 patients and their caregivers. The Advisory Council actively collaborated in designing the trial, including participant eligibility criteria, recruitment materials, incentives for participation, operationalization of the intervention, participant survey materials, and the timing and content of the IVR-T messages. The Advisory Council met 3 times before starting the study and has met at least twice annually during the study itself.

### Eligibility and Recruitment

Consistent with principles of a pragmatic trial, study inclusion criteria are broad, to demonstrate the impact of the intervention in a “real world” setting [24]. Individuals who infrequently seek care or are nonadherent with medications are a specific target of the intervention.

Before the initiation of the trial, the study team developed a hypertension registry using information extracted from FNCH’s electronic medical record, eClinicalWorks (Westborough, MA). FNCH began using eClinicalWorks in 2012. The registry was built using SAS version 9.4 (SAS Institute Inc, Cary, NC). This registry had several purposes, including characterization of the FNCH population, assessment of baseline blood pressure control, and recruitment for the randomized trial. Hypertension was identified using diagnosis codes (ICD-9 401-405; ICD-10 I10-I13, I15), orders for antihypertensive medication, and elevated blood pressures (≥140/90). We considered individuals to have hypertension if any 1 of the following criteria was met: (1) having 2 visits with a hypertension diagnosis on different days, (2) having 1 visit with a hypertension diagnosis and 1 medication order, (3) having 1 visit with a hypertension diagnosis and 1 elevated blood pressure, or (4) having 2 consecutive elevated blood pressures on different days [25]. For study recruitment, we additionally required (1) at least 2 prior visits to FNCH with blood pressure measurements, at least 1 of which took place in the 24 months before recruitment, and (2) aged 21 to 79 years at the time of recruitment. Individuals aged 80 years and above were excluded because of the need to individualize treatment targets in the elderly [6]. Clients were eligible for the study even if their hypertension was under control, with the rationale that even those with controlled hypertension at a single visit may not remain in control over time. We included patients receiving care at FNCH regardless of their racial or ethnic self-identification. Individuals who resided outside Albuquerque (such as rural Indian reservations) were eligible if they identified FNCH as their primary source of care.

Exclusion criteria include the following: another preferred site of primary care, significant impairment of vision and hearing, life-limiting illnesses such as advanced cancer, renal dialysis, receipt of home health care with blood pressure monitoring and/or assistance with administration of medications, hospice services or residence in a nursing home, dementia, pregnancy at the time of recruitment, current homelessness, no landline or cellular phone access, or inability to understand English or Spanish.

Potentially eligible participants were contacted by letter and then by phone. Those who expressed interest completed an in-person baseline visit that included the informed consent process, a baseline survey, and blood pressure measurement using standardized procedures. They were then randomized to either the IVR-T intervention or usual care.

### Randomization

Individuals were randomized 1:1 to IVR-T intervention or usual care using block randomization with blocks of 4. A randomization table was generated by the study statistician (SX) using SAS software. The study coordinators were blinded to the randomization sequence.

### Intervention

Since 2005, the Institute for Health Research at Kaiser Permanente Colorado has developed and managed an IVR-T system that initiates telephone calls to landlines or cellular phones and text messages to cellular phones. The system uses a commercial database to distinguish between cellular phones and landlines and to determine whether a cellular phone is text-enabled [11]. For this intervention, information from the hypertension registry and Research Electronic Data Capture (REDCap) were used to send IVR-T messages to individuals randomized to the IVR-T intervention arm. Individuals in the intervention arm could opt to receive either automated text messages or automated phone calls in either English or Spanish. The messages include reminders of upcoming appointments at FNCH; requests to reschedule recently missed appointments; monthly reminders to refill medications; and weekly motivational messages to encourage self-care, appointment keeping, and medication taking for hypertension (Table 1; Multimedia Appendix 1). The motivational messages for text or telephone were modified from existing messages in the literature [26-29] and tailored with the help of an American Indian psychologist and the FNCH Advisory Council to be culturally appropriate. Some of the messages were recorded by the participants’ primary care clinician at FNCH. Individuals in the IVR-T arm could opt to nominate a care partner to also receive notices of upcoming and missed appointments. Individuals in the IVR-T arm were also offered a home blood pressure monitor. Blood pressure logs were not received or reviewed by the study team. The intervention is unblinded, although participants’ FNCH clinicians were not informed by the study staff of any patient’s group assignment. The protocol for IVR-T messages is shown in Table 1.

**Table 1 table1:** Components of the interactive voice response and text message intervention.

Component	Description
Reminders for upcoming visits	Three days before and 1 day before each upcoming visit
“Recalls” after missed clinic visits	Recall 1 to 6 days after a missed visit
Reminders to refill medications	Monthly reminders to refill hypertension medications
Motivational adherence messages	Weekly, from the list in Multimedia Appendix 1
Inbound calling options	Direct dial options available to participants to reach scheduling staff, a member of the clinical team, or pharmacy to address urgent concerns during business hours

### Study Visits

Participants complete in-person baseline, 6-month, and 12-month visits. At each visit, blood pressure measurements are collected and participants complete a survey. Blood pressure is measured in a standardized fashion during the research visits, using an Omron HEM 907XL IntelliSense Professional Digital Blood Pressure Monitor (an automated sphygmomanometer) [30]. After a 5 min waiting period, blood pressures are taken 3 times, 30 seconds apart. The average of the second and third blood pressures is used. The baseline survey can be self-administered or participants can request assistance from study coordinators. The baseline survey includes questions about general health, blood pressure treatment, adherence to blood pressure medications [31], comorbidities, perceived health competence (adapted from Smith et al [32]), depression (Patient Health Questionnaire-2) [33], discrimination (adapted from several sources [34-36]), health literacy and numeracy (adapted from Brega et al [37]), exercise and diet [38], demographics, and socioeconomic status and social needs (see Multimedia Appendix 2). The 6-month and 12- month visit surveys contain a subset of the questions from the baseline survey, with additional questions about attitudes toward the intervention. Survey answers and other study data are managed using REDCap software. Participants receive US $20 gift cards for each visit.

### Baseline Variables

In addition to information from the baseline survey, we also collected demographic characteristics, hypertension characteristics, comorbidities, and geographic variables using information from the FNCH electronic health record (EHR). Race and ethnicity were categorized using the following hierarchical categories: AI/AN, Hispanic, non-Hispanic white, non-Hispanic African American, non-Hispanic other, and missing. Individuals with missing ethnicity information were assumed to be non-Hispanic.

Comorbidities such as diabetes, cardiovascular disease, and depression were defined as the presence of at least one ICD-9 or ICD-10 diagnosis code within the previous 2 years (see Multimedia Appendix 3). Chronic kidney disease was defined as being present if the most recent estimated glomerular filtration rate in the previous 2 years was less than 60 mL/min/1.73m^2^ using the CKD-EPI estimating equation [39].

Ever homeless was defined using EHR visit types specific to homeless services and include information on visits since the inception of the FNCH EHR in 2012. The multiple insurance payers for FNCH clients were categorized into 5 groups (commercial, IHS, Medicaid, Medicare, and self-pay). We then defined the dominant payer by determining which insurance category predominated over the previous 2 years. When 2 encounters had different insurance categories, we assumed that the insurance change occurred at the midpoint between the 2 encounters. We geocoded addresses and created maps to determine those in and out of the Albuquerque city limits and Bernalillo County limits using ArcMap 10.3.1. (Esri, Redlands, CA) on a secure system. We also mapped the addresses onto census tracks and reported median household incomes and educational levels, using census track information from the 2010 US census. We assessed diet quality using the diet metric from the American Heart Association Simple 7 score and physical activity using American Heart Association recommendations [38].

### Endpoints

The primary outcome of the trial is the change in systolic blood pressure between baseline and 12-month research visits, comparing participants receiving the IVR-T intervention with those in usual care. Secondary outcomes are change in diastolic blood pressure between baseline and 12 months, self-reported adherence, and the proportion of missed clinic appointments.

The primary medication adherence measure is the self-reported Voils instruments administered at baseline and during both follow-up surveys [31,40-42]. The measure has 3 questions about the extent of nonadherence over the previous 7 days; the 5 response options range from missing medication “none of the time” to missing medication “all of the time.” If 1 or more items suggest nonadherence, 21 questions probe reasons for nonadherence; the 5 response options for each question range from being “not at all” a reason for nonadherence to being “very much” a reason. In prior studies, Cronbach alpha for the 3 “extent” items was .84, and the scale correlated significantly with systolic blood pressure and diastolic blood pressure [40]. Although it would have been ideal to corroborate this measure with pharmacy refill adherence or pill counts, FNCH clients use multiple pharmacies that preclude comprehensive assessment of refill adherence [43], and performing regular pill counts was not feasible.

The measure of visit adherence is the proportion of scheduled appointments that are kept, missed, or canceled. This measure is assessed using the FNCH EHR and calculated as a proportion of all visits scheduled during the period from enrollment to the end of follow-up. This is a standard measure in interventional trials to improve appointment keeping [11]. All 3 visit outcomes (kept, missed, and canceled) are important from an operational perspective, as timely visit cancellations allow FNCH to schedule other clients.

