### Analysis Plan

The primary analytic strategy will be intention to treat. As secondary analyses, we will also perform per protocol and as-treated analyses. Linear mixed models will be used to analyze repeated measures of systolic blood pressure (the primary outcome variable) and diastolic blood pressure (a secondary outcome variable) as continuous variables [45]. For each group, the changes from baseline at 6 and 12 months after randomization can be obtained after the linear mixed model is fit and all coefficients are estimated. Then, we will contrast the changes from baseline between the 2 groups to assess the influence of IVR-T intervention on systolic blood pressure and diastolic blood pressure. We also plan to analyze the secondary outcomes missed appointment and medication adherence status using nonlinear mixed models.

We anticipate that some outcomes will be missing because of missed appointments or attrition. By default, the linear mixed models accommodate missing data by assuming that data are missing at random (MAR). We will explore different ways to examine the assumption of MAR [46]. When the data are missing not at random, outcome measures and missingness will be jointly modeled with either random effects selection models or pattern mixture models, whichever is appropriate [47,48]. Multiple imputation methods will also be used to explore the sensitivity of the results to missingness [49].

In our analyses of the baseline data, we compared individuals in the recruitment pool who did and did not enroll in the trial using SAS version 9.4. Statistical significance was computed using Fisher exact test for categorical variables and Mann-Whitney for discrete ordinal variables and continuous variables. A *t* test was used to compare with Mann-Whitney *P* values as a check, and the results were similar except for distance to clinic. Due to outliers for distance to clinic, we report the medians. To compare agreement between the EHR and the study survey for specific comorbidities, we used the prevalence and bias adjusted kappa [50].

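### The missed-appointment outcome has no pre-enrollment counterpart in the described baseline data: the comparison is valid, but it gives up precision that earlier EHR appointment history could probably supply

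*Protocol article*

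**What the plan says.** All references are to the Protocol article.

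- **Outcome.** Under Endpoints, "The measure of visit adherence is the proportion of scheduled appointments that are kept, missed, or canceled". It comes from the FNCH EHR and is "calculated as a proportion of all visits scheduled during the period from enrollment to the end of follow-up".
- **Other endpoints.** Systolic pressure, the primary outcome, is a change from baseline. The same section states: "Secondary outcomes are change in diastolic blood pressure between baseline and 12 months, self-reported adherence, and the proportion of missed clinic appointments". The medication adherence instrument is "administered at baseline and during both follow-up surveys".
- **Baseline data.** Baseline Variables describes the EHR items collected: demographics, hypertension characteristics, comorbidities and geography, with homelessness visits and payer. Prior kept, missed or canceled appointments are not among them. Tables 2 to 4 contain no such row; the nearest is days since the last clinic visit (Table 2).
- **Available history.** Eligibility and Recruitment says "FNCH began using eClinicalWorks in 2012" and requires "at least 2 prior visits to FNCH with blood pressure measurements, at least 1 of which took place in the 24 months before recruitment".
- **Model.** Under Analysis Plan: "We also plan to analyze the secondary outcomes missed appointment and medication adherence status using nonlinear mixed models". Covariates are neither listed nor excluded.

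**The concern.** Appointment keeping is the only endpoint for which the article describes no pre-randomisation value. It is also an outcome that the reminders and recalls act on directly. How often a person missed appointments before enrollment is likely to predict how often they miss them afterwards. Leaving it out keeps that person-to-person variation in the error term, and the reader cannot see how the arms compared on this behaviour at the start. Enrollment reached 295 against an initial target of 512, so precision is worth having where it is cheap.

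The point goes a little beyond an unlisted covariate. Presenting baseline characteristics is one of the article's stated purposes, and the data set it describes does not contain the variable.

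**Working it through.** **1. The plan's own figures.** None is given for the appointment outcome: no expected rate, SD, power or sample size. The stated sample size concerns systolic pressure. With SD 18 mmHg, a 5 mmHg difference, two-sided 5% and 80% power:

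n per arm = 2 × (1.960 + 0.842)² × 18² / 5² = 204 after rounding up, so 408 in total; 408 / 0.80 = 510, against 512 stated.

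That reproduces, but it does not bear on this endpoint.

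**2. Gain from adjusting for the earlier missed proportion.** Inputs: N = 295 (Results); r, the correlation between a person's missed proportions before and after enrollment, is assumed. For a linear model:

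- residual variance factor = 1 − r²
- equivalent sample size = 295 / (1 − r²)
- detectable difference at 80% power, in SD units = 2.802 × √(4/295) × √(1 − r²)

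| Assumed r | Variance removed | Equivalent N | Detectable difference (SD) | Power at an assumed 0.3 SD effect |
|---|---|---|---|---|
| 0 (unadjusted) | 0% | 295 | 0.326 | 0.731 |
| 0.3 | 9% | 324 | 0.311 | 0.771 |
| 0.5 | 25% | 393 | 0.283 | 0.845 |

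The sample-size ratios are 1/0.91 = 1.10 and 1/0.75 = 1.33. All 295 are counted. Anyone with no appointment scheduled in follow-up has no proportion, so the usable number may be smaller.

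**3. Is the unadjusted comparison biased?** The intervention arm has 148 people (Results, in the count of those who accepted a monitor), which leaves 147 in usual care. The standard error of a chance difference in any baseline trait is √(1/148 + 1/147) = 0.116 SD, a 95% range of about ±0.23 SD. The unadjusted standard error already allows for this.

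A simulation of 3,000 trials checked it. It assumed 12 prior appointments and on average 7 follow-up appointments per person, with missed-visit risk varying between people. Per-person proportions were analysed by linear regression with robust standard errors.

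| | Unadjusted | Adjusted |
|---|---|---|
| Type I error, no effect | 0.049 | 0.050 |
| Mean estimate, assumed effect | −0.061 | −0.061 |
| SD of estimate | 0.026 | 0.022 |
| Power | 0.64 | 0.82 |

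Only precision changes. The variance ratio from the unrounded SDs is (0.02173/0.02606)² = 0.695, a 30% reduction. By the formula in step 2 this corresponds to r of about 0.55 (√0.305), slightly above the assumed range, so the simulated power gain is on the favourable side.

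**The case against.** The strongest case against is that nothing here is wrong. Visits scheduled after enrollment are the right window for a randomised contrast, and the article calls the measure standard for trials of this kind. A rate accrued over follow-up needs no baseline value to be valid. Covariates for a secondary model are commonly left to a full protocol or analysis plan, neither of which is shown. All of this stands, and it limits the point to an improvement.

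Four stronger readings are tempting, and the documents do not support them:

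- **That the comparison cannot be corrected for prior behaviour.** If the earlier records exist, they can be extracted at any time before analysis, and the Analysis Plan does not rule this out.
- **That chance imbalance between arms biases the result.** Randomisation is 1:1, and the standard error already reflects chance imbalance. The absence of stratification on prior attendance is not a defect.
- **That Table 2 shows uneven attendance.** The mean of 164.3 days (SD 174.8) is time since the last visit. Someone scheduled once a year who never misses would also show a long gap.
- **That the EHR certainly holds everyone's missed and canceled appointments.** The eligibility rule guarantees at least two earlier visits with blood pressure measured, which are attended visits. Retrievability of the rest is a reasonable inference, since the same EHR supplies the outcome, but it is not stated.

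The size also rests on an assumed r, and the formula is only approximate for a nonlinear mixed model.

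**Conclusion.** The point holds as a low-severity suggestion about precision on one secondary outcome. It is neither an error in the definition nor a source of bias. The article's baseline data contain no measure of earlier appointment keeping, while the other endpoints have baseline values and the same record system probably holds this one. The likely gain is a 9% to 25% reduction in residual variance. It depends on three conditions: that past missed and canceled appointments are retrievable, that r lies between 0.3 and 0.5, and that the linear-model result carries over roughly to the planned model. The gain will be smaller for people with few earlier appointments.

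**What to change.** 1. Confirm that past scheduled, missed and canceled appointments can be retrieved from the EHR.
2. If so, extract them in both arms for a fixed look-back before randomisation, for example 24 months, by the same definition as the outcome, and report them by arm.
3. Before appointment outcomes are examined by arm, prespecify the prior missed proportion, together with the number of prior scheduled visits, as a covariate in the nonlinear mixed model for missed appointments.
4. Do not use a change from the earlier period. Eligibility required an attended visit within 24 months of recruitment, so the look-back is selected towards kept visits.

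The post-enrollment outcome window stays as it is. The cost is one further EHR query and one covariate, with no participant contact. The drawback is an imprecise baseline proportion for people with few earlier appointments.
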